### The intervention group

The authors have developed and tested a unique smartphone-based monitoring and treatment system, the Monsenso system, for patients with bipolar disorder. The Monsenso solution was initially developed by the IT University in Copenhagen in close collaboration with the Copenhagen Affective Disorder Research Center (CADIC), Psychiatric Center Copenhagen, Mental Health Services, Capital Region of Denmark, and a wide range of patients, clinicians, and researchers (in the EU funded MONARCA project [28, 29], the MONARCA II trial [30], and the RADMIS trial [31]). The effects of the Monsenso smartphone system in patients with bipolar disorder have so far been investigated in three RCTs by the authors [29–31]. Overall, using the smartphone-based monitoring system resulted in increased quality of life, decreased perceived stress, and increased use of Lithium without influencing the degree of depressive or manic symptoms.

Following the MONARCA studies and the RADMIS trial, adjustments to the Monsenso system were made, which now provides the following main features:Offer patients and clinicians across the Mental Health Services in the Capital Region of Denmark a tool for digital monitoring and support of treatment as a common way to substitute the general use of paper-based week schemes and clinical questionnaires.Make psychoeducation, personal treatment plans, and cognitive behavioral therapy tools easily assessable via smartphone as self-help between clinical appointments.Collecting time series of data consisting of daily self-monitoring (mood, activity, sleep, irritability, mixed mood, cognitive problems, anxiety, alcohol consumption, stress, medicine consumption, menstruation, notes) and clinical questionnaires as well as sensor data from smartphone aiming to:◦ Provide an overview of clinical status, behavior, and adherence to and effect of medication and psychological therapy◦ Use data to intensity research in CAG bipolar clinics◦ Gain insight into psychopathology and treatment on sub-group levels (e.g., according to age and gender, bipolar subtype I or II)◦ Optimize ongoing work with algorithms to predict relapse and episodes

The patients included in the SmartBipolar trial are invited to conduct smartphone-based evaluations in the Monsenso system daily. Patients in the intervention group and the first control group are invited to conduct evaluations of symptoms daily. Patients in the second control group are invited to conduct daily monitoring of mood only. In the two control groups, a study nurse without interfering in any way with the patients’ treatment will continuously monitor the adherence to smartphone-based self-monitoring, and in the case of lacking self-monitoring, the patients will during the entire trial period be contacted and encouraged to fill in the data. Both the intervention group and the control groups are using their smartphones for the 6-month trial period. In the SmartBipolar trial, the Monsenso system is available for smartphones capable of collecting sensor-based data on measures of illness activity on various levels (e.g., different levels according to type of smartphone—versions of Android smartphones and iPhones).

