### Objectives

The objectives are as follows: to investigate in a randomized controlled parallel-group trial whether (1) daily smartphone-based outpatient monitoring and treatment *including* clinical feedback versus (2) daily smartphone-based monitoring *without* clinical feedback or (3) daily smartphone-based mood monitoring *only* improves mood instability in patients with bipolar disorder and, furthermore, to investigate if daily smartphone-based monitoring, *including* clinical feedback, improves *questionnaire-based* quality of life, self-rated depressive symptoms, self-rated manic symptoms, perceived stress, and satisfaction with care, as well as *register-based* risk of psychiatric hospitalization and cumulated days of psychiatric admission as compared with daily smartphone-based monitoring *without* clinical feedback and daily smartphone-based mood monitoring *only* in patients with bipolar disorder. In addition, this is to investigate if daily smartphone-based monitoring, *including* clinical feedback, improves *smartphone-based* measures of stress, anxiety, irritability, activity, sleep duration, days with adherence to medication, days without mixed mood, and adherence to smartphone-based monitoring as compared with daily smartphone-based monitoring *without* clinical feedback in patients with bipolar disorder.

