#### Subjective (self-monitored) measures of illness activity in the intervention group

The patients randomized to the intervention group are prompted by an alarm in the Monsenso system at a self-chosen time during the day (standard 7 pm but can be changed and also be de-activated by the patient) to evaluate subjective measures of illness activity daily. The following subjective (self-monitored) measures of illness activity are available for evaluation: mood (scored from depressive to manic on a scale from − 3, − 2, − 1, − 0.5, 0, + 0.5, + 1, + 2, + 3), sleep duration (number of hours slept per night, measured in half-hour intervals), medicine intake (taken as prescribed/taken with changes/not taken), activity level (scored from very low to very high on a scale from − 3, − 2, − 1, 0, + 1, + 2, + 3), mixed mood (yes/no), irritability (scored from not present, present to some degree, present, present most of the time on a scale from 0, 1, 2, 3, 4), anxiety (scored from not present, present to some degree, present, present most of the time on a scale from 0, 1, 2, 3, 4), cognitive problems (scored from not present, present to some degree, present, present most of the time on a scale from 0, 1, 2, 3, 4), alcohol consumption (number of units consumed per day, 0 to + 10 scale), stress (scored from not present, present to some degree, present, present most of the time on a scale from 0, 1, 2, 3, 4), menstruation for women (yes/no), a number (unlimited) of personal parameters (created by the patients themselves), and a free-text note. A patient can edit their responses in a self-assessment until midnight and the latest given response will be saved and shown in the web portal. If the patients wish to change their self-reports, they can enter a second evaluation in addition to the initial one, and both of the subjective evaluations are then visible for the patient and the healthcare provider when logging on to in the Monsenso system. If the patients forget to evaluate the subjective measures, they can evaluate retrospectively for up to two days. Pictures of the self-reported mood monitoring are presented in Figs. 2 and 3.

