#### The clinical feedback

By offering all patients with bipolar disorder and clinicians to use the system, a unique world class data set is made, which can be used to optimize treatment to the benefit of patients and clinicians. Nevertheless, it is unclear and has never been investigated how smartphone-based treatment is best optimized—with or without a clinical feedback loop. The clinical feed-back loop includes (1) that clinicians continuously monitor self-reported patient smartphone data making early intervention possible when data suggest deterioration; (2) actively support and help patients employing the Monsenso tools including psychoeducation, personal treatment plans, and cognitive behavioral therapy tools; (3) integration of the Monsenso system in group-based psychoeducation courses in the CAG bipolar clinics; and (4) meetings with the staff from the entire CAG bipolar clinic on a weekly basis where Monsenso registrations are monitored and discussed in collaboration (board meetings).

It is possible that patients will be able to use the Monsenso system entirely as a self-help tool in addition to treatment in the CAG bipolar clinics (see first control group below).

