#### Tertiary outcomes (based on daily smartphone-based measures)

The following outcomes will be compared between the intervention group and the first control group.Mean stress (per month during the trial)Mean anxiety (per month during the trial)Mean irritability (per month during the trial)Mean activity (per month during the trial)Mean sleep duration (per month during the trial)Percentage of days with mixed moodPercentage of days with adherence to medication during the trial periodAdherence to smartphone-based self-monitoring during the trial period

No changes in outcome measures have been made after trial commencement. All patients will be contacted by the study nurse during the study to ensure retention and complete follow-up.

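### Missing self-monitoring is chased by a study nurse in the control groups only, so the adherence comparison with the first control group partly measures the trial's own reminders

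*Protocol article*

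**What the plan says.** The procedure is in the protocol article under The intervention group. The sentence opens "In the two control groups, a study nurse without interfering in any way with" the patients' treatment, and gives that nurse continuous oversight of self-monitoring adherence. It then states the action: "in the case of lacking self-monitoring, the patients will during the entire trial period be contacted and encouraged to fill in the data".

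The outcome is in the section on tertiary outcomes. The list is introduced by "The following outcomes will be compared between the intervention group and the first control group", and its last item is adherence to self-monitoring over the trial period. The Objectives section makes this a question about feedback: the intervention is to improve "adherence to smartphone-based monitoring as compared with daily smartphone-based monitoring" without clinical feedback.

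Three other statements bear on the point:

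- The clinical feedback, for the intervention group: "clinicians continuously monitor self-reported patient smartphone data making early intervention possible when data suggest deterioration". Clinicians also support use of the tools, and staff discuss the registrations at weekly meetings.
- Tertiary outcomes, after the list: "All patients will be contacted by the study nurse during the study to ensure retention and complete follow-up".
- Subjective measures in the intervention group: a daily alarm that the patient can switch off, and "If the patients forget to evaluate the subjective measures, they can evaluate retrospectively for up to two days".

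**The concern.** A comparison of adherence between two arms shows an effect of clinical feedback only if nothing else that acts on adherence differs between them. Here something else does. Staff contact aimed at missed entries is added to the comparator for the whole six months, and it is a trial procedure rather than part of the condition being compared. A null or negative adherence result could then mean that feedback does not help patients keep up monitoring, or that nurse reminders worked about as well as feedback. The planned data cannot separate the two.

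There is a possible second route, to the primary outcome. rMSSD uses only pairs of consecutive days. If a reminded patient fills in a missed day from memory, and the recalled value resembles the day of entry, day-to-day differences shrink. If that happened more often in the control groups, the primary contrast would shrink with it.

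**Working it through.** **1. Is the chasing really unequal?** Setting the passages side by side:

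| Text | Arms | Aimed at missed daily entries? |
|---|---|---|
| Nurse oversight and contact | Two control groups | Yes, explicitly |
| Clinician monitoring in the feedback loop | Intervention | No; aimed at deterioration |
| App alarm | Described for intervention | Automatic prompt, can be switched off |
| Nurse contact for retention | All | Not stated; general follow-up |

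Only the first row is human follow-up of missing self-monitoring, and it names the control groups. If the general retention contact already covered missed daily entries in every arm, there would be no need to single out the control groups.

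**2. Effect on the adherence contrast.** The protocol gives no figure to reproduce: neither adherence by arm nor the yield of reminders. Let a_I and a_C be adherence without reminders, and r the share of missed days recovered in the first control group (all assumed). Then

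observed control adherence = a_C + r(1 - a_C)

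observed difference = a_I - a_C - r(1 - a_C)

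For example, at 85% in both arms and r = 0.10: 0.85 - 0.85 - 0.10 × 0.15 = -0.015.

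| a_I / a_C | True difference | r = 10% | r = 25% | r = 50% |
|---|---|---|---|---|
| 85% / 85% | 0 | -1.5 | -3.75 | -7.5 |
| 80% / 70% | +10 | +7.0 | +2.5 | -5.0 |
| 90% / 80% | +10 | +8.0 | +5.0 | 0 |

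Differences are in percentage points. A true difference vanishes when r = (a_I - a_C)/(1 - a_C): for 80% versus 70%, 0.10/0.30, or one third of missed days.

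**3. Could the primary outcome move?** Assume that mood follows a first-order autoregression with day-to-day correlation ρ, that a random fraction f of days is back-filled in the control groups beyond what happens in the intervention group, and that each such day is an exact copy of the next entered day. The ratio of rMSSD with copying to rMSSD without it is then

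√[(1 - f)/(1 - fρ)]

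A simulation over 180 days agrees with this to about 0.001.

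The Introduction reports 87-95% compliance with this system, so 5-13% of days would be missed. The table applies the formula to the protocol's mean of 0.80.

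| Share of days back-filled | f | Fall in units, ρ = 0.5 | Fall in units, ρ = 0.2 |
|---|---|---|---|
| Half of missed days, 95% compliance | 0.025 | 0.005 | 0.008 |
| Half of missed days, 87% compliance | 0.065 | 0.014 | 0.021 |
| All missed days, 95% compliance | 0.05 | 0.010 | 0.016 |
| All missed days, 87% compliance | 0.13 | 0.028 | 0.044 |

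The range is about 0.005 to 0.04 units, or 2.5% to 22% of the 0.20 target. Its upper end needs every missed day recovered and every recovered value an exact copy.

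**The case against.** The intervention group is not left alone. Clinicians follow its data continuously, staff review registrations weekly, and all patients have some nurse contact. Nurse follow-up in the control groups can be seen as a reasonable counterpart that protects data completeness where no clinician is watching, which matters for an outcome that needs consecutive days. On that view the contrast compares feedback with nurse-supported monitoring, and because the distortion runs against the intervention, a positive result would stand.

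Much of this is fair. The contrast is not meaningless, and an observed advantage for feedback could not be credited to the reminders. But prompting by clinicians belongs to the randomized treatment, whereas the nurse's reminders are a trial procedure added to the comparator. Feedback versus nurse reminders is not the question in the Objectives, and a null or negative result stays ambiguous.

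A reader might also infer that back-filling lowers rMSSD in the control groups alone and by a substantial part of the target. The protocol does not support that. The two-day rule is described under the intervention group, so those patients can back-fill too, and its use in the control groups is itself an inference. Copying of the current day appears nowhere in the text. An extra 10-20% of back-filled days, which would give up to about 0.07 units, mostly exceeds the 5-13% of days that the reported compliance leaves missing.

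Finally, deleting the outcome from an unblinded trial with 150 of 201 patients included would invite a charge of outcome switching. That stands, and the outcome should therefore be kept in the report.

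**Conclusion.** The point holds for the adherence contrast. As described, follow-up of missing entries is unequal by design, it acts directly on a tertiary outcome that is also an objective, and it pushes the comparison against the intervention. The amount cannot be computed; a spurious -1.5 to -7.5 points rests on the assumed 85% adherence and 10-50% recovery.

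It does not show that the primary analysis is compromised. An effect on rMSSD needs more back-filling in the control groups than in the intervention group and recalled values close to the current day, neither of which the protocol documents. Even with exact copying, and compliance as in the earlier studies, it is about 0.005 to 0.04 units. Compliance could be lower in this trial, so a check is worthwhile, but the protocol gives no ground for attributing a null primary result to this mechanism.

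**What to change.** - Keep adherence to self-monitoring in the report, as a descriptive process measure with the number of nurse contacts per arm beside it. State that it is not evidence for or against an effect of clinical feedback.
- Reword the Objectives so that adherence is described by arm rather than tested as something feedback improves, and align the tertiary outcome list. Record the change and its reason, with a date, before any comparison by arm.
- If the app stores the date of each entry, report the share of retrospective entries by arm and add a sensitivity analysis of rMSSD on same-day entries only. The primary analysis stays as it is.

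Equalising the follow-up of missing entries now would come late: only 201 - 150 = 51 patients remained to be recruited when the article was written.

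The cost is that one tertiary outcome is no longer tested as an efficacy outcome, and the sensitivity run has fewer usable day-pairs. Nurse contacts must be logged or recovered from existing records. No extra patients are needed.

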#### Subjective (self-monitored) measures of illness activity in the intervention group

The patients randomized to the intervention group are prompted by an alarm in the Monsenso system at a self-chosen time during the day (standard 7 pm but can be changed and also be de-activated by the patient) to evaluate subjective measures of illness activity daily. The following subjective (self-monitored) measures of illness activity are available for evaluation: mood (scored from depressive to manic on a scale from − 3, − 2, − 1, − 0.5, 0, + 0.5, + 1, + 2, + 3), sleep duration (number of hours slept per night, measured in half-hour intervals), medicine intake (taken as prescribed/taken with changes/not taken), activity level (scored from very low to very high on a scale from − 3, − 2, − 1, 0, + 1, + 2, + 3), mixed mood (yes/no), irritability (scored from not present, present to some degree, present, present most of the time on a scale from 0, 1, 2, 3, 4), anxiety (scored from not present, present to some degree, present, present most of the time on a scale from 0, 1, 2, 3, 4), cognitive problems (scored from not present, present to some degree, present, present most of the time on a scale from 0, 1, 2, 3, 4), alcohol consumption (number of units consumed per day, 0 to + 10 scale), stress (scored from not present, present to some degree, present, present most of the time on a scale from 0, 1, 2, 3, 4), menstruation for women (yes/no), a number (unlimited) of personal parameters (created by the patients themselves), and a free-text note. A patient can edit their responses in a self-assessment until midnight and the latest given response will be saved and shown in the web portal. If the patients wish to change their self-reports, they can enter a second evaluation in addition to the initial one, and both of the subjective evaluations are then visible for the patient and the healthcare provider when logging on to in the Monsenso system. If the patients forget to evaluate the subjective measures, they can evaluate retrospectively for up to two days. Pictures of the self-reported mood monitoring are presented in Figs. 2 and 3.

**Fig. 2 Fig2:**
[figure not shown]
Screenshot of the smartphone-based self-assessment

**Fig. 3 Fig3:**
[figure not shown]
Screenshot of the web portal used by the clinicians for the feedback

#### Smartphone-based cognitive behavioral therapy (CBT) modules

Within the Monsenso system, the following CBT modules are available: psychoeducation, behavioral activation, cognitive restructuring, and rumination-focused CBT [41]. The psychoeducation and mood-monitoring system include strategies for detecting and intervening with early signs of relapse. Patients are encouraged to use the module in an individualized and sequential way according to their condition, affective state, and insight and following guidance from the study nurse if wanted. The behavioral activation module includes activity monitoring and activity scheduling and focus on regulation of sleep and daily routines. The cognitive restructuring includes simple techniques to help patients to identify and modify dysfunctional automatic thoughts. A main purpose of the smartphone-based CBT modules was to help patients to reduce depressive ruminations. Therefore, a specific rumination-focused CBT strategy was included.

#### The clinical feedback

By offering all patients with bipolar disorder and clinicians to use the system, a unique world class data set is made, which can be used to optimize treatment to the benefit of patients and clinicians. Nevertheless, it is unclear and has never been investigated how smartphone-based treatment is best optimized—with or without a clinical feedback loop. The clinical feed-back loop includes (1) that clinicians continuously monitor self-reported patient smartphone data making early intervention possible when data suggest deterioration; (2) actively support and help patients employing the Monsenso tools including psychoeducation, personal treatment plans, and cognitive behavioral therapy tools; (3) integration of the Monsenso system in group-based psychoeducation courses in the CAG bipolar clinics; and (4) meetings with the staff from the entire CAG bipolar clinic on a weekly basis where Monsenso registrations are monitored and discussed in collaboration (board meetings).

It is possible that patients will be able to use the Monsenso system entirely as a self-help tool in addition to treatment in the CAG bipolar clinics (see first control group below).

### The control group

#### The first control group

Patients allocated to the first control group are invited to conduct daily smartphone-based monitoring *without* a clinical feedback loop. Furthermore, they will have full access to the smartphone-based CBT modules as described above.

#### The second control group

Patients allocated to the second control group are invited to conduct daily smartphone-based mood monitoring only.

##### Sensor-based data

Smartphones capable of collecting sensor-based data on measures of illness activity regardless of randomization group (intervention group or control group) collects as many sensor data daily during the trial period as possible based on patient given consent (iOS and Android: Battery level, Step count, Activity, Geolocation. Android: Light and screen state (on, off)). Thus, we will be able to investigate the use of sensor-based data for prediction analyses etc.

All included patients continue with their treatment at the CAG bipolar clinic. After the end of the SmartBipolar trial, patients will be offered the full version of the Monsenso system including clinical feedback.

### Assessments

Since the SmartBipolar trial is a pragmatic trial and patients are recruited from the CAG bipolar clinics, all patients are diagnosed with bipolar disorder by highly trained clinicians with specific expertise within bipolar disorder. All outcomes, apart from registry-based measures, which are based on public registry-based data blinded for intervention, are based on patient evaluations (questionnaires and smartphone-based evaluations) and therefore assessed without blinding to the intervention. The patients are, regardless of randomization group, enrolled for a 6-month trial period and invited to fill out questionnaires two times during follow-up—at baseline and after 6 months (Table 1). Data collection of basic sociodemographic, clinical data, and outcome measures (besides the primary and registry-based data) including questionnaires will be handled electronically via the Redcap database in accordance with the standard procedure in the Capital Region of Denmark.

